### Secondary outcomes

The following will be evaluated as secondary outcomes: 1. episodes of violence in school measured through two scales for evaluating bullying suffered and bullying perpetrated in the last 30 days [30] and 2. current psychiatric symptoms (anxiety, depression, hyperactivity and current behavior and symptoms of eating disorders) [31, 32] [33].

### Mediators

As mediators of program effectiveness, the following will be evaluated: 1. normative beliefs; 2. positive beliefs and negative beliefs about alcohol and marijuana use; 3. knowledge about drugs; 4. decision-making skills; and 5. refusal skills [34]. The scales for each mediator are described in Table 1.

In addition to the modules covering primary outcomes, secondary outcomes and mediators, the questionnaire also has a module on sociodemographic data. The socioeconomic class will be evaluated through the ABEP (Brazilian Market Research Association) scale [35] (Table 1**).**

### Intervention

In each of the experimental schools, all 8th grade students will receive the program #Tamojunto2.0, and the school will assign one teacher per class to receive training on the program.

The #Tamojunto2.0 program will be applied to students in the classroom by trained teachers. The 12 lessons, described in Table 3, use interactive methods and will be guided by student and teacher handbooks. On average, the lessons last 50 min each. The program consists of four lessons on attitudes and knowledge about drugs, four lessons on social and interpersonal skills, and four lessons on personal skills. Each lesson will have three to five activities addressing life skills [13, 38]. The teacher’s handbook provides information about each lesson’s procedures, objectives, required materials, activities to be followed and tips. Both handbooks are freely accessible and can be found in several languages at www.eudap.net.

**Table 3 Tab3:** Description of the 12 lessons in the *#*Tamojunto 2.0 program, including their title, activities and goals

Lesson	Title	Activities	Goals
**1**	#Tamojunto introduction	▪ Presentation ▪ Group work: coexistence contract management ▪ Homework	Introduction to the program, establishment of rules for the lessons and reflection on what is known about drugs
**2**	Where do I belong?	▪ Situation play ▪ Game discussion	Clarify the influences and expectations of the group
**3**	Choices: protective and risk factors for alcohol use	▪ Information on different factors influencing drug use ▪ Discussion and work in small groups	Information on different factors influencing drug use
**4**	What do you think reflects reality?	▪ Presentation ▪ General discussion ▪ Group work ▪ Game	Encourage critical analysis of information, reflection on differences between personal opinions and actual data, reassessment of norms
**5**	What we know and do not know about smoking	▪ Quiz ▪ General discussion ▪ Feedback ▪ Game	Information on the effects of smoking, differentiation of expected vs. real effects and short-term vs. long-term effects
**6**	Express yourself	▪ Game ▪ Discussion and plenary ▪ Group work	Proper communication of emotions, distinction between verbal and nonverbal communication
**7**	Manifest yourself in the world and in your life	▪ General discussion ▪ Group work ▪ Role play	Promote assertiveness and respect for others
**8**	The new guy!	▪ Role play ▪ Game ▪ General discussion of the class	Recognition and appreciation of positive qualities, acceptance of positive feedback, practice and reflection on how to get to know new people
**9**	Drugs—educate yourself	▪ Group work ▪ Question and answer game	Information on the positive and negative effects of drug use
**10**	Coping strategies	▪ Presentation ▪ General discussion ▪ Group work	Expression of negative feelings, dealing with challenges
**11**	Problem solving and decision-making	▪ Presentation ▪ General discussion ▪ Group work ▪ Homework	Problem solving and fostering creative thinking and self-control
**12**	Setting goals and final considerations	▪ Game ▪ Group work ▪ General discussion	Distinguish the long-term and short-term goals, evaluate the program and its process

In Brazil, the English materials were translated into Portuguese, with adaptation of idiomatic expressions and the substitution of information about heroin for information about crack, as well as changes in the lessons addressing alcohol use [28]. The new adaptation, created in 2018, removed the changes made to the alcohol use lessons during the years 2014 and 2015 and changed class 3 on alcohol back to its original form (i.e., the European model) to remove the possible iatrogenic cultural adaptations regarding alcohol use [16]. Therefore, in this protocol, we describe a study that will be carried out in the years 2019 and 2020 to evaluate the revised version of the #Tamojunto program [16], now called #Tamojunto 2.0.

The teachers who will administer the program will be trained in a 16-h training program conducted by professionals from the BMH. In addition, the implementation will be accompanied by two on-site visits by BMH professionals throughout the 12 lessons and by a virtual forum where teachers can post questions about the application of the activities in the lessons.

### Data analysis of the randomized controlled trial

The data will initially be analyzed by a descriptive analysis, that is, qualitative variables will be summarized as numbers and percentages and numerical variables as means, standard deviations, medians, minima and maxima. Descriptive analyses will be performed for different patterns of drug use. This dataset will be used to calculate sample weights through the svy command in Stata so that the baseline data analysis can be presented in an expanded form, aiming at correcting for losses and extrapolating the data to the sample universe [39, 40].

All analyses will be carried out in the two samples: “intention to treat” (ITT), which will include all the participating classes that received at least one lesson of the program, and “per protocol” (PP). The PP analysis will include only those classes that receive the complete protocol (12 lessons), determined based on evaluating the dose and fidelity form that will be completed by the teacher at the end of each lesson.

Because the data are collected in groups, they are not independent at two levels (school and class), and the measures of association should be analyzed through GLLAMM (Generalized Linear Latent and Mixed Models), which calculates the level of dependence between the data [41]. Due to the hierarchical structure of the data, multilevel models will be used to simultaneously test for differences in the prevalence of outcomes between times and between groups, considering schools as a modeling level (Gllamm Stata 14). All analyses will be adjusted by sex, socioeconomic level and site. The analyses will be performed in Stata 15 (descriptive analyses and multilevel GLLAMM), and a significance level of 5% will be adopted.

Structural equation modeling (SEM) will be used to analyze the mediators involved in reducing the primary and secondary outcomes over 18 months [42] (Fig. 2) and to assess the effectiveness of the intervention in changing the behavioral patterns of adolescents related to drug use and violence through latent transition analysis (LTA). LTA can be understood as a longitudinal extension of latent class analysis, as it is used to identify and describe the ideal number of classes representing the study population, following their transition over a given period [43]. This approach offers great advantages compared to traditional logistic regression methods in longitudinal studies, such as a lower rate of false discovery compared to multilevel logistic regression models when assessing the effects of an intervention on multiple outcomes [44]. Drug use is often studied with the latent class model due to the high correlation observed between the different drugs used, addressing the heterogeneity of drug use behavior in adolescents [45]. These analyses will be performed with the Mplus 8 software, and a significance level of 5% will be adopted.

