### Study design

A randomized controlled trial with two parallel groups (intervention and control) will be conducted to evaluate the effectiveness of the program for adolescents enrolled in 8th grade middle school in 70 public schools in three Brazilian cities, totaling approximately 6300 students distributed in 210 groups. Randomization will be conducted at the school level. Schools randomly selected to be part of the intervention group will offer the 12 lesson #Tamojunto2.0 program in the year 2019. Schools in the control group will not offer prevention programs or activities in 2019. The selection of schools and the allocation to the control or intervention group will be performed by a simple random draw from the list of the National Institute for Educational Studies and Research ‘Anísio Teixeira’ (INEP), which includes all schools from each municipality.

The baseline data (T1) will be collected two weeks before implementation of the program in February/March 2019, and the follow-up data will be collected at 9 months (T2) in November/December 2019 and at 18 months (T3), August/September 2020 after the initial data collection in August 2020. The data will be collected simultaneously for both groups. This protocol was prepared in accordance with SPIRIT 2013 [22], and the study will be conducted according to the CONSORT guidelines [23].

At the end of each lesson, all teachers in the experimental classes will complete a fidelity and dose form, stating which of the planned activities were or were not taught in the lesson and if the teacher made any changes. Figure 1 shows the study design flowchart.

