### Randomization

Schools from each of the participating municipalities registered in the INEP’s national registry of schools will be randomly selected. The schools must meet the following inclusion criteria: (a) a public school and (b) have at least three 8th grade classes. Thirty schools will be drawn in Fortaleza, 30 schools in São Paulo and 10 schools in Eusébio. Among the schools selected to participate in the study, a second random draw will define which schools will be included in the control group and which will be included in the experimental group, maintaining a ratio of 1:1 in the number of control and experimental schools in each municipality. After selecting the schools, a list with the names of the selected schools will be forwarded to each education department of the participating municipalities to request authorization for participation in the study. Due to the involvement of the government, all schools typically agree to participate, as occurred in a previous study [16].

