Some limitations of this study must be noted. The main limitation is related to the known high rate of school absences of the Brazilian student population, which could result in bias. However, this is a common limitation to longitudinal studies [48–50], and the goal is to try to minimize it by giving prior notice to the students about the researchers’ visit for data collection, which did not occur in previous versions of the study [16]. Another limitation of the study is that the information is obtained through self-reporting by the students themselves. Although this method may lead to measurement bias, self-reporting is the most recommended evaluation method for adolescents and has been found to have excellent validity in studies evaluating drug-related behaviors [51, 52]. Currently, there are no viable alternatives for collecting data on alcohol use in adolescent samples, as biological measures would not be appropriate in a sample in the early stages of alcohol use [53]. To avoid the overreporting of drug use, a question of the use of fictitious drugs (holoten and carpinol) has been added to the questionnaire to screen this problem. In cases where the student responds positively to these drugs, the questionnaire will be excluded from the study, reducing the information bias [54].

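### The set labelled intention to treat requires at least one delivered lesson, so it is a modified ITT set, and no analysis of all randomised schools as allocated is defined

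*Protocol article*

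**What the plan says.** Under Study design, the Protocol article states: "Randomization will be conducted at the school level". Under Randomization, a second draw assigns the selected schools, "maintaining a ratio of 1:1 in the number of control and experimental schools in each municipality". The control condition is an absence of programme: "Schools in the control group will not offer prevention programs or activities in 2019".

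Under Data analysis of the randomized controlled trial, the article names the analysis sets: "All analyses will be carried out in the two samples". The first is called intention to treat and is described as one "which will include all the participating classes that received at least one lesson of the program". The second is per protocol and keeps only classes that were taught all 12 lessons, judged from the teacher's form. That form exists in one arm only: "all teachers in the experimental classes will complete a fidelity and dose form". The article does not say how control classes enter either set, and it names no third set.

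**The concern.** Intention to treat means that every randomised unit is analysed in the arm to which it was allocated, whatever happened next. Here, entry depends on a lesson being delivered. That event comes after randomisation and can happen in one arm only. An intervention class whose teacher never begins is dropped. A control class in a comparable school has no matching test to fail, so it stays.

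Classes that never begin may differ from the rest in student drug use. If they do, removing them from one arm shifts the comparison without any programme effect. Two features of this trial make that important. It is meant to support a decision on expanding the programme as public policy, and failure to start is part of what a policy delivers. In addition, the Background reports that the previous version raised alcohol initiation, so an analysis that could produce or hide a difference by selection is unwelcome.

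This is not a detail left to a statistical analysis plan. The article states a definition, and the definition does not match its label.

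**Working it through.** **1. Does any stated set keep all randomised schools as allocated?**

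| Set | Entry rule, intervention arm | Entry rule, control arm |
|---|---|---|
| Called ITT | at least one lesson delivered | not stated; no lessons exist |
| PP | all 12 lessons delivered | not stated; no lessons exist |

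All analyses use one of these two. An intervention class with zero lessons is in neither, so the answer is no.

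**2. Reproducing the plan's power.** Inputs from Sample size calculation: 35 schools per arm, 90 students each, 10% against 7.5%, intraclass correlation (ICC) 0.005, 5% significance (taken as two-sided).
- Design effect = 1 + (90 − 1) × 0.005 = 1.445.
- Effective n per arm = 3150 / 1.445 = 2180.
- Power = 83.2% (pooled z), 82.2% (t, 68 df) or 81.8% (continuity correction). The stated 82% is reproduced. The sample size is not at issue; these inputs are reused below.

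**3. How large could the bias be?** No non-start rate is given, so take a share f of intervention schools as an assumption, with prevalence q, no true effect and 10% overall prevalence:

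spurious benefit = 0.10 − (0.10 − f × q) / (1 − f)

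The protocol's own ICC limits q. The between-school SD is √(0.005 × 0.10 × 0.90) = 2.1 points. Assume school prevalences follow a beta distribution with mean 0.10 and ICC 0.005, that is a + b = 1/0.005 − 1 = 199, giving a = 19.9 and b = 179.1. Then suppose the non-starters are exactly the highest-prevalence schools:
- f = 10%: the top tenth averages q = 14.0%. Kept prevalence = (0.10 − 0.0140) / 0.90 = 9.55%. Spurious benefit is about 0.45 points, or 0.45 / 2.5 = 18% of the target.
- f = 20%: the top fifth averages q = 13.1%. Kept prevalence = (0.10 − 0.0262) / 0.80 = 9.22%. Spurious benefit is about 0.78 points, or 0.78 / 2.5 = 31% of the target.

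If the non-starters were instead the lowest-prevalence schools, the sign reverses. The bottom tenth averages 6.6% and the bottom fifth 7.2%, giving spurious harm of about 0.38 and 0.70 points by the same formula. At f = 0 the bias is zero.

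**4. What a true ITT analysis costs in power.** If the effect is 2.5 points where the programme starts and nil elsewhere, the ITT difference is 2.5 × (1 − f):

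| f | Difference (points) | Power |
|---|---|---|
| 0% | 2.50 | 83.2% |
| 5% | 2.375 | 79.0% |
| 10% | 2.25 | 74.3% |
| 20% | 2.00 | 63.6% |

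**The case against.** The strongest reply is that the rule may never remove anyone. The Intervention section plans delivery to all 8th graders in experimental schools, supported by 16 hours of teacher training, two site visits and a virtual forum. The Randomization section says schools typically agree to take part because government is involved. If every class delivers one lesson, the stated set and a true ITT set coincide. This stands as a limit on the size of the problem. It does not repair the definition, and the protocol itself expects uneven delivery: the fourth hypothesis and the per-protocol set both presuppose it.

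Three stronger readings are tempting and are not supported.

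- **The rule removes the whole control arm.** A literal reader might infer this, since no control class receives a lesson. But the same section plans tests of differences between groups, so the rule can only be meant for intervention classes.
- **The bias could equal the full 2.5-point target.** That needs, for example, 20% of schools not starting, with 20% prevalence against 7.5% in the rest. This split alone implies a between-school variance of 0.2 × 0.10² + 0.8 × 0.025² = 0.0025 and an ICC of 0.0025 / 0.09 = 0.028, more than five times the stated 0.005.
- **The fictitious-drug exclusion is a second break of the same kind.** The article says: "In cases where the student responds positively to these drugs, the questionnaire will be excluded from the study". This is a validity screen applied alike in both arms. Nothing in the lesson descriptions links the programme to answers about invented drugs, and keeping flagged reports would retain answers that the screen marks as invalid.

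**Conclusion.** The definition is wrong as written. What the article calls intention to treat is a modified ITT set whose filter can act in the intervention arm only, and no analysis of all randomised schools as allocated is defined. This affects every planned comparison, because all analyses run in this set or in the per-protocol set.

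The resulting bias is conditional. It arises only if some intervention classes deliver no lesson and those classes differ in drug use. Its direction cannot be known in advance: nothing in the article shows that non-starters are higher-risk. The figures of 0.45 and 0.78 points rest on assumed non-start shares of 10% and 20% of schools, perfect selection of the highest-prevalence schools, a beta distribution and the protocol's ICC. Under those assumptions they are upper illustrations, not estimates. The article gives no class-level variation, and since the rule works on classes, large variation between classes could change the figures.

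**What to change.** - Define ITT as all eligible 8th-grade students in all 70 randomised schools, analysed in the arm to which the school was allocated, whatever the number of lessons delivered, including zero. Name it the primary analysis set.
- State that classes which never start are still surveyed at T2 and T3, within the visits already planned for both groups.
- Rename the at-least-one-lesson set modified ITT and make it supplementary. State how control classes enter it and the per-protocol set.
- Report the number of intervention classes with zero lessons.

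The change is mainly one of wording; design, sample size and data collection are otherwise untouched. The cost is dilution if some classes never start: when non-starters gain nothing, power falls from about 83% to about 74% at 10% non-start. If all classes start, nothing is lost.

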### Participants

Eighth-grade middle school students aged 12 to 14 years, enrolled in public schools from three Brazilian cities (Fortaleza, Eusébio - northeastern region - and São Paulo - southeastern region) will participate in the effectiveness evaluation of the program. The participating cities were recommended by the BMH, based on the identification of the municipalities in which there was already collaboration and a partnership with the local government for the application of the #Tamojunto2.0 program*.* In addition, the selected cities have large sociodemographic differences; the two cities in the northeast are poorer and less populous than São Paulo, which is the fifth most populous city and the tenth richest city in the world.

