### Sample size calculation

The PASS 15.0 software was used to calculate the sample sizes of the two intervention groups in a cluster randomized design [24]. A sample size of at least 3150 adolescents in the control group and 3150 in the intervention group, distributed among 35 clusters (schools) with at least 90 subjects in each arm, will reach a power of 82% in identifying a difference between groups of 2.5% for the outcome of binge drinking in the past month, with an initial prevalence of 10%, a significance level of 5%, and an intraclass correlation of 0.005. Thus, it is necessary to ensure the inclusion of at least three 8th grade classes from each sampled school, with 35 schools in the intervention group and 35 in the control group. Therefore, 70 schools will be selected to ensure a minimum sample size of 6300 adolescents, considering possible losses to follow-up.

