### Instrument

The instrument to be used for data collection in evaluating the program effectiveness was designed using instruments previously used in studies evaluating the effect of drug prevention programs both in Brazil [16, 25] and abroad [14]. One of the instruments used as a base was created by the EU-DAP (European Drug Addiction Prevention Trial) and used in a previous effectiveness evaluation of Unplugged [26]. In Brazil, this instrument has been translated and adapted into Portuguese [27], with some questions replaced by questions adopted from two questionnaires widely used in several studies among Brazilian students: the World Health Organization questionnaire used in the VI Brazilian Survey of Drug Use among Students [28] and the National Survey of School Health questionnaire used by the Ministry of Health [5]. Details of the instrument are presented in Table 1.

**Table 1 Tab1:** Details of the instrument to be applied among the students at the evaluation time points

Variable	Main Use *	Source	Scale
Drug use in lifetime (first use, incidence and prevalence), past year and past month (prevalence)	Primary outcomes (alcohol, tobacco, marijuana, inhalant, cocaine, crack and amphetamine use and binge drinking)	CEBRID [28]	22 dichotomous questions
Socioeconomic class	Confounder	ABEP [35]	A scale with 15 items
Demographic data	Confounders	CEBRID [28]	2 questions (age and sex)
Decision-making	Mediator	EUDAP [26]	A scale with 9 dichotomous items
Positive and negative beliefs	Mediator		Two scales with 11 dichotomous items each (one for alcohol and one for marijuana)
Normative beliefs	Mediator		Two scales: a Likert scale with 4 items and a dichotomous scale with 11 items
Knowledge about drugs	Mediator		A scale with six items
Refusal skill	Mediator		A scale with three items
School violence	Secondary outcome	Olweus Bully Victim Questionnaire [30]	Two scales: a scale to measure violence perpetrated with eight dichotomous items each and a scale to measure violence suffered with seven dichotomous items each
Psychiatric symptoms	Secondary outcome	Strengths and Difficulties Questionnaire [31]	A scale with 25 dichotomous items
Eating disorders	Secondary outcome	SCOFF [33]	A scale with 5 dichotomous items

The form that evaluates dose and fidelity (Table 2), to be completed at the end of each lesson by the experimental group teachers, was prepared based on the EUDAP instrument [29].

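### Age is listed as a confounder in Table 1 but is missing from the adjustment set fixed for all analyses; adding it is a minor improvement at almost no cost

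*Protocol article*

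**What the plan says.** The section on data analysis of the randomized controlled trial closes the covariate list: "All analyses will be adjusted by sex, socioeconomic level and site". In the Instrument section, Table 1 gives each variable a main use. Two rows are marked as confounders: socioeconomic class, and demographic data, the latter described as "2 questions (age and sex". The table's title, "Details of the instrument to be applied among the students at the evaluation time points", places these questions at every wave, so age is available at baseline. The Participants section describes the cohort as "Eighth-grade middle school students aged 12 to 14 years".

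Under Randomization, schools are allocated 1:1 within each municipality; no balancing on age is mentioned. The planned model is multilevel, with school as a level, and compares prevalence between times and between groups. Incidence (new cases) is also a primary outcome. Every analysis is to be run in two samples: one of classes that received at least one lesson, and one of classes that received all 12.

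**The concern.** Two current statements in one article disagree. An analyst who follows Table 1 puts age in the model; one who follows the analysis section leaves it out. The analysis section does not defer the choice to a later document: it fixes the list for all analyses. Sex, from the same row of Table 1, is kept, while age is dropped without comment.

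Three things could be at stake: precision, protection against a chance difference in mean age between two arms of 35 schools, and control of confounding where the analysed sample is selected after randomisation. An unresolved covariate also leaves room to choose the model after the data are seen.

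**Working it through.** **1. The plan's own figure.** The Sample size calculation section plans 35 schools of 90 students, so 3150 students, per arm. It aims to detect "a difference between groups of 2.5% for the outcome of binge drinking in the past month", starting from 10%; the ICC (intraclass correlation) is 0.005 and the level 5% (taken as two-sided).

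- Design effect: 1 + (90 − 1) × 0.005 = 1.445. Effective size: 3150 / 1.445 = 2180 per arm.
- For 10% against 7.5%, mean prevalence is 0.0875. The standard error is √(2 × 0.0875 × 0.9125 / 2180) = 0.0086, or 0.86 points.
- Power: Φ(0.025 / 0.00856 − 1.96) = Φ(0.96) = 83.2%. With a t distribution on 68 degrees of freedom it is 82.1%. The stated 82% is reproduced.

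**2. Precision gained by adding age.** The article gives no age distribution and no association of age with any outcome, so both are assumed: mixes over ages 12/13/14 of 10/70/20, 20/60/20 and equal thirds, and an odds ratio per year of 1.3 to 2.5. At 10% prevalence, age then explains R² = 0.2% to 4.3% of the variance. Approximating the gain by effective n / (1 − R²), power goes from 83.2% to 83.3%–84.8%, a gain of about 0.1 to 1.6 points.

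**3. Chance imbalance in a single wave.** Two routes, both on assumed inputs.

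*(a) From an assumed SD of school mean age.* With SD 0.2 years, the standard error of the arm difference is 0.2 × √(2/35) = 0.048 years, and 2 SE is 0.096. The shift in prevalence is 0.10 × 0.90 × ln(OR) × 0.096:

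- OR 1.5 per year: 0.09 × 0.405 × 0.096 = 0.35 points.
- OR 2 per year: 0.09 × 0.693 × 0.096 = 0.60 points.
- Letting the SD run from 0.1 to 0.3 gives about 0.2 to 0.9 points.

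*(b) From the age mixes in step 2 and an assumed school-level ICC of age from 0 to 0.10.* The imbalance is 1.96 × SD(age) × √(2/3150 × (1 + 89 × ICC of age)), which is 0.03 to 0.13 years.

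- Low end: 0.027 years × slope 0.0237 per year = 0.06 points.
- High end: 0.127 years × slope 0.0742 per year = 0.94 points.

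Together the range is roughly 0.1 to 0.9 points.

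**4. Check against the planned ICC.** School differences in mean age contribute (slope × SD of school mean age)² / 0.09 to the outcome's ICC.

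| Assumption | Contribution | Share of 0.005 |
|---|---|---|
| SD 0.2, OR 1.5 | (0.0365 × 0.2)² / 0.09 = 0.0006 | 12% |
| SD 0.2, OR 2 | (0.0624 × 0.2)² / 0.09 = 0.0017 | 35% |
| SD 0.3, OR 2 | (0.0624 × 0.3)² / 0.09 = 0.0039 | 78% |

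At the upper end, age alone would account for most of the between-school variation that the plan assumes from all causes.

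**5. Where the shift would act.**

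- *Prevalence, group by time.* An age difference between arms exists at T1 as well as at T2 and T3. If the effect of age on the log odds is about constant over time, it largely drops out of the group-by-time contrast.
- *First use.* Students at risk are non-users at T1, so no baseline level of the outcome can absorb the imbalance. No size is computed because the article gives neither an incidence nor a target difference for it.
- *Samples defined by lessons received.* Both are selected after randomisation. If delivery is related to the age mix of a class, age is a confounder there in the ordinary sense.

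**The case against.** The strongest reply is that randomisation already deals with this. Schools are allocated at random, so the whole-sample estimate is unbiased on average whether or not age is in the model. Between-school variation due to age belongs to the school-level variance, which the planned model and the ICC of 0.005 both include. A chance shift is therefore part of the standard error, not an addition to it. The single-wave shift in step 3 is also not the planned prevalence contrast, which has a baseline wave. All of this stands.

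A reader might infer that the omission biases the main result, costs appreciable power, or distorts the effect by the 14% to 24% of the 2.5-point target that 0.35 and 0.60 points represent. The documents support none of these. Those percentages describe an unlucky draw in one unadjusted wave, the power change is at most about 1.6 points under the assumed effects, and nothing in the article shows that age strongly predicts drug use within a single grade.

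It can also be said that Table 1 describes a questionnaire and is not a model specification: site is adjusted for but does not appear there. That weakens the contradiction but does not remove it, since the table's stated use for age is as a confounder.

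The reply does not cover first use among baseline non-users or the samples formed after randomisation.

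**Conclusion.** The inconsistency is real; its consequence is minor. Age is labelled a confounder and then dropped from a list that applies to all analyses, without a reason. The whole-sample comparison remains valid, and the precision at stake is about 0.1 to 1.6 points of power. The omission matters mainly for first use among baseline non-users and for the samples defined by lessons received. Whether age confounds in those samples is a possibility that the documents neither show nor exclude, and adjusting for age would not by itself repair selection after randomisation.

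The range of 0.1 to 0.9 points describes a roughly 2 SE imbalance in a single wave of past-month binge drinking at 10% prevalence. It rests on assumed age mixes, school-level clustering of age and odds ratios per year. Its upper end sits badly with the planned ICC. It should be read as a plausible limit on bad luck, not as an expected bias. This is a free improvement, not a fault that undermines the primary analysis.

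**What to change.** In the adjustment sentence of the analysis section, insert *age at baseline* ahead of sex, so that the set is age at baseline, sex, socioeconomic level and site, in agreement with Table 1. If age was left out on purpose, give the reason there and change its label in Table 1. Settle this before outcome data are analysed by arm.

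The cost is one phrase. Age is already in the questionnaire at baseline, and one more covariate with about 6300 students has a negligible downside.
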